### Hypotheses

The PRCI increases the use of positive reappraisal coping strategies and reduces symptoms of general anxiety and depression, improves quality of life across assessment (pre intervention, intervention and post intervention) as well as increases positive and decreases negative emotions during the fourteen days of the waiting period in patients undergoing an IVF/ICSI treatment.

### Study measures

Data will be obtained with self-reported questionnaires, daily monitoring and from the treatment medical records. Table 1 shows the assessment timetable. Questionnaires will be completed prior to, during and after the intervention whereas monitoring will be daily during the two-week waiting period. The following self-report measures will be used:

The Background Information Form (BIF) is a 16-item questionnaire to measure demographic (e.g. age, educational status), medical (e.g. previous illness) and gynaecological (e.g. infertility diagnosis, previous infertility treatment) characteristics as well as treatment expectations (e.g. chances of conceiving, perceived control over the outcome).

The Hospital Anxiety and Depression Scale (HADS) will be used to measure general anxiety and depression. The HADS consists of 14 items (7 items for each subscale) that are rated on a 4-point Likert scale. The total score is the sum of the 14 items, and for each subscale the score is the sum of the respective seven items (ranging from 0–21). Scores on each scale can be interpreted in ranges: normal (0–7), mild (8–10), moderate (11–14) and severe (15–21). The Dutch version of the HADS has been shown to be a valid and reliable instrument [28].

The Fertility Quality of Life (FertiQoL) scale will be used to measure the impact of infertility and its treatment. FertiQoL consist of 36 items that assess core (24 items) and treatment related quality of life (10 items) and overall life and physical health (2 items). Items are rated on a 5-point response scale. Cronbach reliability coefficients for the Core and Treatment FertiQoL were 0.92 and 0.81, respectively [29]. The convergent validity of the Dutch version of the FertiQoL has been investigated and shows similar reliability [30]. Items are summed and scaled, with a range of 0 to 100. Higher scores indicate better quality of life.

The Ways of Coping Questionnaire (WCQ) will be used to measure use of coping strategies. The WCQ is based on the cognitive stress and coping model of Lazarus and Folkman [31,32]. The instrument is designed to measure situation-specific coping. The 41 items of the Dutch version are rated on a 4-point response scale that, when summed, yields 6 subscales. Taking responsibility (6 items), problem solving (8 items), social support (6 items), wishful thinking (8 items), avoidance (7 items), positive reappraisal (6 items). The Cronbach alpha coefficients reported for the six subscales ranges from 0.65 to 0.80. To measure the concurrent validity the WCQ has been compared with the seven scales of the Utrecht Coping List with good correspondence between these [33].

The Intervention evaluation form (IEF) is a 24-item questionnaire developed to assess intervention feasibility, acceptability and effects, which was used to assess PRCI in previous research [1]. It measures the following aspects of the intervention: practicality (6 items), acceptability (4 items), endorsement (4 items), perceived psychological effects (8 items) and perceived duration of intervention effects (2 Items).

The Daily Record Keeping (DRK) sheet will be used daily to rate reactions to the 14-day waiting period (PRCI Intervention and Monitoring Control groups only). The DRK comprises 46 possible reactions to the IVF waiting period, including 20 emotions, optimism and pessimism about pregnancy, 12 physical symptoms, five appraisals, and seven coping strategies. The emotional subscale is based on the theory of Lazarus and Folkman [20] and contains affective reactions that are averaged to produce anxiety (i.e., tense, nervous, worried), depression (i.e., anger, frustrated, sad) and positive affect (i.e., happy, content, fulfilled). The five coping strategies are measured with Stone and Neale’s [34] daily coping measure namely strategies of distraction, positive redefinition, problem-focused, seeking emotional support and acceptance. The twelve physical symptoms list two common side effects of medication (i.e., abdominal discomfort, spotting), two symptoms related to treatment success/failure (e.g., breast tenderness, menstrual cramps) and the remaining eight symptoms originate from the physical stress reactions (e.g., racing heart, muscle tension) of the Pennebaker Inventory of Limbic Languidness (PILL) [1]. Subscale scores were created (where relevant) by averaging across subscale items and higher scores indicate more of the attribute (e.g., more tension, breast tenderness, distraction). Participants will be instructed to complete the DRK at the end of the day, and for the PRCI intervention group at least one hour after reading the PRCI card to limit the chance of DRK ratings being artificially and transiently influenced by completing the DRK.

The DRK has been shown to be acceptable for monitoring during protracted periods of treatment with 15% attrition during 75 days of monitoring and 9% over a period of 30 days [9]. The reported Cronbach alpha ranges from 0.70 – 0.82 for subscales [2]. The DRK was translated and used in a Dutch study [22] that showed good correspondence between the original and Dutch version, and acceptable convergent and discriminant validity with other measures of anxiety and depression. The DRK was also tested in a feasibility study in a population from the recruitment clinic in the Netherlands showing acceptability and feasibility (unpublished data, [name]).

A medical chart review at the end of treatment will be used to obtain treatment data and will include the total number of past IVF/ICSI stimulated and cryopreserved cycles, past intrauterine insemination cycles, previous conceptions/births, infertility diagnosis, smoking status, alcohol use, and body mass index. Data about the current treatment will include: type of treatment and protocol, date of first and subsequent treatment attempt, treatment cancellation (yes/no) and reason for cancellation, number of oocytes retrieved, total number of embryos created, transferred and cryopreserved, treatment outcome (positive pregnancy test, clinical pregnancy, live birth), physician recommendation for next cycle and patient compliance with physician recommendation”.

### Statistical analysis

IBM SPSS Statistics will be used to perform the statistical analysis. Equivalence of baseline measures between groups will be examined by one-way analyses of variance (ANOVA) for normally distributed variables on interval or ratio level, chi-square for normally distributed variables on nominal level and Kruskal Wallis *H* test for normally distributed variables on ordinal level. If study variables are not normally distributed then data will be transformed to normalise (e.g., square root, log, etc. as is required). If the groups are not comparable on demographics, medical history or gynaecological variables, those variables will be employed as covariates in subsequent analyses. To examine the differences between groups over time a repeated measure mixed factorial ANOVA design will be used for variables on interval or ratio level. To compare the fourth group with the three separate groups also an ANOVA design will be used. Intention to treat and multi-level modelling will be used to analyse the data to take account of attrition.

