### Sample size

The sample size calculation for the three-arm RCT is based on the following parameters. To test the difference on anxiety between three groups using a mixed factorial ANOVA, power of 95%, α = 0.05 and a medium effect size a total of 297 subjects was required (99 patients per group) [24,25]. However, taking into account a 20% attrition rate at least 124 women will be recruited in each group. Effect size and attrition were derived from Lancastle and Boivin [1]. The addition of the fourth group only slightly modified sample size and 110 participants were recruited to the fourth group.

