### Randomization

Stratified randomization of the 372 women into one of the three groups will be performed by using a computer-generated table of random numbers. The type of treatment (stimulated or cryopreserved IVF/ICSI) will stratify the population because emotions and expectations relative to a stimulated IVF/ICSI may differ from a cryo-preserved treatment [26,27]. Randomization will take place after the first assessment (Time 1 pre-intervention) between follicle aspiration and embryo transfer. An independent research nurse will be responsible for the randomization. Double blinding will take place for participants and clinic staff. Participants will not be told what intervention is being evaluated. The researcher will have no contact with participants after randomization. All women will receive written information about group assignment on the day of the embryo transfer. They will receive instructions for the waiting period in an opaque sealed envelope after the embryo transfer. The clinical staff that performs the embryo transfer will be blinded for the content of the envelope. After the embryo transfer, there will be no further contact between the clinical staff, other patients, or the researcher during the 14-day waiting period.

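### Covariates are chosen by testing baseline balance, so chance sets the adjustment model and the stratification factor tends to be left out of it

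*Protocol article*

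**What the plan says.** The Statistical analysis section of the protocol article begins with baseline testing: "Equivalence of baseline measures between groups will be examined by one-way analyses of variance (ANOVA"), with chi-square and Kruskal-Wallis tests for nominal and ordinal variables. One covariate rule follows, and it is the only one in the article: "If the groups are not comparable on demographics, medical history or gynaecological variables, those variables will be employed as covariates in subsequent analyses". No threshold is given for declaring groups not comparable.

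The main analysis is a repeated-measures mixed factorial ANOVA of group differences over time. Multi-level modelling is also named, to deal with attrition. Neither sentence lists covariates.

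The Randomization section gives the stratification factor and its reason: "The type of treatment (stimulated or cryopreserved IVF/ICSI) will stratify the population because emotions and expectations relative to a stimulated IVF/ICSI may differ" from those of a cryopreserved cycle. It also places randomisation after the Time 1 assessment.

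**The concern.** Under sound randomisation, baseline differences between the three arms arise by chance, so testing them cannot show which variables predict anxiety. A variable unrelated to the outcome that happens to differ is adjusted for. A strong predictor that happens to be balanced is not. The terms of the model stay unknown until the data are in, and with no threshold stated, the decision is also open to judgement.

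The rule also works against the design. Treatment type was stratified on because it was expected to relate to emotions. Stratification is meant to balance it, and a rule that admits only unbalanced variables will then tend to keep it out.

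At stake are a prespecified analysis and the precision that prognostic covariates could add.

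**Working it through.** **1. The plan's own sample size.** Inputs from Sample size: "power of 95%, α = 0.05 and a medium effect size a total of 297 subjects was required (99 patients per group"), for a test described as "To test the difference on anxiety between three groups using a mixed factorial ANOVA". The article gives no number for a medium effect; I assume Cohen's f = 0.25. For the group-by-time interaction with 3 groups and 3 times, df1 = 4, df2 = 2(N − 3) and λ = f²N.
- Power at N = 297 is 94.8%. N = 300 is needed for 95%, so the stated 297 reproduces to within 3%.
- Attrition: 99 / (1 − 0.20) = 123.75, so 124 per group, and 3 × 124 = 372, as stated.

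The sample size is not in dispute. The calculation matters here because it is the interaction test that reproduces the stated number.

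**2. How often chance adds a covariate.** Assume a 0.05 level and independent tests. P(at least one) = 1 − 0.95^k.

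| Variables tested (k) | P(at least one) |
|---|---|
| 5 | 23% |
| 10 | 40% |
| 16 | 56% |
| 20 | 64% |

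The article does not fix k. The Background Information Form has 16 items, some of them on treatment expectations, which the rule does not cover. The chart review adds others.

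**3. Leaving out the stratum, for a between-group comparison of one score.** Assume 30% cryopreserved cycles and a stratum effect b in within-stratum SD units. Share of variance R² = 0.21b² / (1 + 0.21b²), with 0.21 = 0.3 × 0.7. Equivalent unadjusted N = 297 / (1 − R²). SE ratio = 1/√(1 − R²). The last two columns are the simulated type I error of the three-group F test (3,000 runs, Monte Carlo SE about 0.004).

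| b | R² | Equivalent N | SE ratio | Stratum ignored | Stratum included |
|---|---|---|---|---|---|
| 0.3 | 1.9% | 303 | 1.009 | 0.056 | 0.058 |
| 0.5 | 5.0% | 313 | 1.026 | 0.047 | 0.053 |
| 0.8 | 11.8% | 337 | 1.065 | 0.034 | 0.050 |

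Ignoring a strong stratum makes the test conservative. In the same runs, with five candidate covariates, selecting them by baseline test gave type I error between 0.033 and 0.052, so there is no inflation.

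**4. Power, and where the gain applies.** Illustrative inputs, none from the documents: two arms compared, 99 per group, difference 0.3 SD, two-sided 0.05, error variance pooled over three arms (294 df). Noncentrality = 0.3 × √(99/2) / σ, where σ is the residual SD.
- One post-baseline score, no covariate: σ = 1, noncentrality 2.11, power 56%.
- Same, always adjusted for a covariate correlated 0.5 with the score: σ = √0.75, noncentrality 2.44, power 68%.
- Same covariate under the adjust-only-if-significant rule: 55% to 57% in simulations of 6,000 runs, hardly better than no adjustment.
- Change from Time 1 to Time 2, correlation between times 0.5: change variance 2(1 − 0.5) = 1, so power is 56%. Adding a covariate with the same effect at both times leaves it at 55% (simulated), because the effect cancels in the difference.
- Time 2 as the outcome with Time 1 as covariate, correlation 0.5: variance 1 − 0.25 = 0.75, power 68%.

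**The case against.** The strongest objection is that the plan's main test is of differences over time, and there a time-constant covariate changes nothing. That stands. A reader might infer that the rule costs the primary analysis about 12 points of power. The documents do not support this, because that figure belongs to a between-group comparison of a single post-baseline score.

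Four further points stand in whole or in part.
- A reader might say that baseline anxiety is ignored. It is not: Time 1 is already a level of the repeated factor.
- A reader might take treatment type to be known to be prognostic and deliberately excluded. The Randomization section says only that emotions may differ, and the analysis section is silent on the factor. A condensed article may leave model terms to a fuller document. The point survives because the one stated rule works against including the factor.
- The chance argument does not cover the non-randomised PRCI Control group. Its imbalances may be systematic, and removing all adjustment there would be wrong.
- A reader might infer from "chi-square for normally distributed variables on nominal level" that the wrong tests are planned. Nominal data cannot be normal, but chi-square for nominal and Kruskal-Wallis for ordinal variables are the usual matches. This is a wording slip.

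It can also be said that the conditional rule does no worse than no adjustment. That is true of power and type I error, but the model would still be unsettled until the data are seen.

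**Conclusion.** The point holds in limited form. The article states a covariate rule, so this is not a detail left to an analysis plan, and the rule selects on chance imbalance in the randomised arms. Its consequences are a model not fixed in advance (23% to 64% chance of at least one chance covariate for 5 to 20 variables) and lost precision in between-group comparisons of post-baseline scores. For the stratum alone the loss is modest: standard errors about 1% to 7% larger across the assumed effects. Type I error is not inflated.

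The figures rest on assumptions the article does not supply: the 0.05 threshold, independent baseline tests, a 30% cryopreserved share, the stratum effects, the correlations of 0.5 and the 0.3 SD difference. The criticism of the rule itself depends on none of them. The stated 297 and 372 are unaffected.

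**What to change.** For the three randomised arms:
- Describe baseline characteristics without hypothesis tests and delete the conditional rule.
- Prespecify treatment type (stimulated or cryopreserved) in the model, with a short fixed list from data already collected, for example age and number of previous cycles.
- If the Time 1 score is to be a covariate, model Time 2 and Time 3 as the outcomes and adjust for Time 1 where such a score exists. Do not enter Time 1 as both response and covariate. Treatment outcome has no Time 1 score and needs only the fixed list.

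For comparisons with the PRCI Control group, keep confounder adjustment, using a prespecified list not chosen by significance.

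Correct the phrase that calls nominal and ordinal variables normally distributed.

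Cost: no new data, no change in sample size, a few degrees of freedom, and a small change of model if Time 1 becomes a covariate.

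### Daily emotion ratings: the ANOVA wording does not say which effect decides, a group-by-day reading can miss a steady PRCI benefit, and the covariate rule leaves the pre-randomization rating unused

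*Protocol article*

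**What the plan says.** All places are in the Methods/Design part of the Protocol article.

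- **Statistical analysis** names one method for repeated outcomes on an interval or ratio scale: "To examine the differences between groups over time a repeated measure mixed factorial ANOVA design will be used". It does not mention the daily record separately, does not say whether the group main effect or the interaction is the treatment test, and does not mention sphericity. It adds: "Intention to treat and multi-level modelling will be used to analyse the data to take account of attrition". Covariates enter only by one rule: background characteristics (demographic, medical-history or gynaecological) on which the groups turn out to be unequal.
- **Study measures**: "The Daily Record Keeping (DRK) sheet will be used daily to rate reactions to the 14-day waiting period", in the PRCI Intervention and Monitoring Control groups only.
- **Table 1** also lists a one-day DRK at T1 for all groups. The daily DRK begins only in the waiting-period column.
- **Randomization**: "Randomization will take place after the first assessment (Time 1 pre-intervention) between follicle aspiration and embryo transfer". The T1 one-day DRK is therefore a true baseline. Allocation is stratified by stimulated or cryopreserved treatment.
- **Hypotheses**: the PRCI "increases positive and decreases negative emotions during the fourteen days of the waiting period".
- **Objective** lists emotions in the waiting period among the secondary outcomes.

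**The concern.** One sentence has to serve two kinds of series. The HADS is measured at T1, T2 and T3, and T1 precedes randomization, so a group-by-time interaction is a natural treatment test there. The daily DRK series has no pre-intervention day: the card is in the envelope given out after embryo transfer, and all 14 ratings come later. A card that shifts mood by the same amount every day produces a group difference in level and no group-by-day interaction.

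A reader who carries the HADS logic over to the daily record would therefore test the wrong effect for one plausible form of the hypothesis. With both effects available and no rule, the choice could also be made after the data are seen.

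Two further points follow. The group-by-day F has 13 numerator degrees of freedom and assumes sphericity, which fails if adjacent days are more alike than distant ones. And the one rating that could sharpen the comparison, the T1 one-day DRK, has no stated role. The Discussion gives the daily record and the Monitoring Control group the task of isolating the card's specific effect on the waiting period, so this analysis matters although the outcome is secondary.

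**Working it through.** **1. The plan's own figure.** Sample size section: 95% power, α = 0.05, a medium effect (taken as Cohen's f = 0.25; no figure is given), 297 women, 99 per group. A group-by-time test for 3 groups × 3 times has df1 = 4, df2 = 2(N − 3) and λ = f²N. At N = 297, λ = 0.0625 × 297 = 18.56, df2 = 588 and power is 0.948; 0.95 is reached at N = 300. A one-way ANOVA would need 252. The figure is thus reproduced within about 1% by an interaction test, which suggests, but does not prove, that the interaction was in mind for the primary outcome. Attrition: 99/0.8 = 123.75, rounded up to 124; 3 × 124 = 372, as stated.

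**2. Assumptions for the daily series.** The article gives no correlations or effect sizes for the DRK. Assumed: n = 99 per group, 14 days, daily SD 1, constant between-woman share of variance π = 0.3 or 0.5, and AR(1) correlation ρ = 0.4 to 0.8 for the remainder.

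**3. Interaction under a steady benefit.** If the group difference is δ on every day, each day's deviation from the mean difference is δ − δ = 0. The interaction sum of squares carries no signal at any sample size, so its power equals its false-positive rate. In simulation with δ = 0.4, the Greenhouse–Geisser-corrected test rejected in 4.4–5.6% of trials.

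**4. Group main effect of the same ANOVA.** The 14-day mean has variance v = π + (1 − π) × (average of ρ^|j−k| over all pairs of days). The F test on 1 and 196 df has λ = (n/2)δ²/v. Example, π = 0.5, ρ = 0.8: v = 0.724, λ = 49.5 × 0.16/0.724 = 10.94, power 91%.

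**5. T1 one-day DRK as covariate.** T1 is treated as one further day just before day 1 in the same correlation model, with correlation r to the 14-day mean. Then λ becomes λ/(1 − r²), with 195 error df. Same example at δ = 0.25: λ = 49.5 × 0.0625/0.724 = 4.27 (power 54%); r = 0.748, 1 − r² = 0.44, λ = 9.7 (power 87%).

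| π | ρ | v | Main effect, 0.4 SD | r | 0.25 SD unadjusted | 0.25 SD with T1 | Uncorrected interaction, no effect |
|---|---|---|---|---|---|---|---|
| 0.3 | 0.4 | 0.409 | 99% | 0.52 | 78% | 89% | 7.1% |
| 0.3 | 0.6 | 0.473 | 98% | 0.55 | 72% | 86% | 8.2% |
| 0.3 | 0.8 | 0.613 | 95% | 0.63 | 61% | 82% | 12.0% |
| 0.5 | 0.4 | 0.578 | 96% | 0.69 | 63% | 89% | 6.7% |
| 0.5 | 0.6 | 0.624 | 94% | 0.70 | 60% | 87% | 9.9% |
| 0.5 | 0.8 | 0.724 | 91% | 0.75 | 54% | 87% | 11.6% |

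Power columns are from the formulas; the last column is simulated. A separate simulation over the same range of assumptions gave 56–81% rising to 81–90% for the two 0.25 SD columns.

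**6. False positives.** The uncorrected interaction rejects in about 5% of null trials when there is no serial correlation, 6% at ρ = 0.3, 8% at 0.5, 10–11% at 0.7, 12% at 0.8 and 14–15% at 0.9. A constant within-woman correlation alone causes no inflation. With Greenhouse–Geisser the rate was 4–6% throughout.

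**7. Sensitivity for T1.** T1 falls between hCG and embryo transfer, so its correlation with the waiting-period mean may be weaker than in step 5. The equivalent gain in women is 1/(1 − r²): 1.19 at r = 0.4 and 1.56 at r = 0.6. From 60% unadjusted power this gives 68% and 79%. Adding T1 as a 15th level of the time factor does not do the same job: at 0.3 SD the corrected interaction then has power 0.13–0.41, against 0.90–1.00 for the T1-adjusted 14-day mean (π from 0 to 0.5, ρ from 0.3 to 0.9).

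**The case against.** - **The named method does detect a steady benefit.** A mixed factorial ANOVA yields a group main effect as well as an interaction, and nothing restricts the test to the interaction. This stands. A reader might infer that the plan will miss a steady benefit; the document supports only that it can, if the interaction is the effect read.
- **Nothing says the test is uncorrected.** This also stands. A reader might infer an inflated error rate, but the article is silent, and a sphericity correction is a detail an article commonly leaves to the full plan. The inflation is conditional.
- **Multi-level modelling is planned.** True, and such a model can carry day-to-day correlation. But it is tied to attrition, and the text does not say whether it replaces the ANOVA or which of the two decides.
- **The hypothesis does not specify a constant gap.** Correct. The Background says that distress rises during the wait and that the card was better at sustaining positive reappraisal coping, so a gap that changes over the days is plausible. The interaction is worth reporting; it should not be the only route to a finding.
- **Omitting a baseline covariate is valid in a randomized comparison.** Agreed. The T1 point concerns precision, not bias. Treatment type might be counted as a medical variable, but under the stated rule it would enter only if the groups differed on it, which stratification is meant to prevent.

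**Conclusion.** The point holds in limited form. The general ANOVA sentence reaches a 14-day series with no pre-intervention day and does not fix the deciding effect. Read as group-by-day, the test is blind to a steady benefit (about 5% corrected power), while the main effect of the same ANOVA has 91–99% power at 0.4 SD. Inflation to about 6–12% arises only if the interaction is left uncorrected and correlation decays with lag (ρ from 0.3 to 0.8).

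The firmest part is the covariate rule. As worded, it gives no place to the pre-randomization DRK rating or to the randomization stratum. Using the T1 rating would raise power for 0.25 SD from roughly 55–80% to roughly 80–90% under the assumed correlations, and by less if T1 tracks the waiting period weakly. All correlations and effect sizes are assumptions. The outcome is secondary, and the documents do not support a claim that the planned analysis is invalid.

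**What to change.** For the daily DRK scales in the PRCI Intervention and Monitoring Control groups, state in the Statistical analysis section that:

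- the already planned multi-level model will be fitted to days 1–14, with group, day, group-by-day, treatment type (the stratum) and the same-scale T1 one-day DRK score, the last two as prespecified covariates whether or not the groups differ on them;
- the within-woman covariance will allow day-to-day correlation, for example a random intercept plus AR(1), or unstructured;
- the PRCI minus Monitoring difference averaged over the 14 days is the deciding contrast, and group-by-day is a supporting description of shape.

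The cost is wording. The T1 rating is already collected and the model can be run in the named software. The small downside is that a day-specific pattern becomes secondary.

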The decision to add the PRCI Control after the RCT has the disadvantage that this group will not be randomized. However, the group will allow us to estimate PRCI effects independent of daily monitoring, in case monitoring has an unexpected intervention effect that interacts with PRCI effects. Our RCT procedures use written protocols and blinding which should minimise the chance of systematic bias even in this non-randomized group with respect to attributes that may affect the dependent variables. The expected sample size will provide adequate power for detection of effects, determined from previous studies using the PRCI tool.

A limitation of this study is the method used for recruiting the participants. The opt-in method was employed to recruit on the advice of the Ethics Committee. In this method participants are sent an invitation to the trial and themselves contact the team to take part, which differs from the more conventional opt-out approach where all patients are contacted about the trial unless they have contacted the team to indicate that they do not wish to be approached. Although the opt-out method improves recruitment, the ethical committee often does not approve this method because repeated contact is too burdensome for participants [37,38]. In the study of Junghans at al. [37] there was a difference in risk factors between the two methods. Patients in the opt-in arm had fewer risk factors (44%) compared to patients in the opt-out arm (60%) (P = 0.053).

Another limitation could be the participation of only one hospital. We choose to recruit in only one hospital because this university hospital attracts patients from all over the country. However, as there is collaboration with other clinics nationwide inferences about the generalizability of findings can be determined via comparison of patient characteristics collected as part of wider collaborations.

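### The non-randomised PRCI Control group is compared with the randomised arms by ANOVA with only imbalance-triggered adjustment, on a bias reassurance that does not follow, and no stated contrast shows whether monitoring modifies the PRCI effect

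*Protocol article*

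**What the plan says.** - **Analysis.** The Statistical analysis section plans a repeated-measures mixed factorial ANOVA for group differences over time, then adds: "To compare the fourth group with the three separate groups also an ANOVA design will be used". In the same section, demographic, medical-history or gynaecological variables become covariates if the groups turn out not to be comparable on them. Intention to treat and multi-level modelling are there to deal with attrition.
- **Purpose.** The opening of Methods/Design explains that daily monitoring might itself act as an intervention and so weaken, strengthen or mask the PRCI effect. The Discussion says the group allows the PRCI effect to be estimated free of monitoring, "in case monitoring has an unexpected intervention effect that interacts with PRCI effects".
- **Bias.** The Discussion concedes that lack of randomisation is a disadvantage, then cites "written protocols and blinding which should minimise the chance of systematic bias even in this non-randomized group".
- **Timing.** Methods/Design says the decision to add the group came while the RCT was recruiting. The Discussion says the group was added after the RCT.
- **Size.** For the three-arm RCT, "taking into account a 20% attrition rate at least 124 women will be recruited in each group", starting from 99 evaluable per group. For group 4, "The addition of the fourth group only slightly modified sample size and 110 participants were recruited to the fourth group". The Discussion follows its text on group 4 with "The expected sample size will provide adequate power for detection of effects", naming no comparison.

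**The concern.** Everyone in group 4 receives the PRCI, so there is no random sequence to conceal, and nothing in the design balances who enters the group or when. Written protocols and blinding standardise information, procedures and reporting. They cannot make a separately recruited cohort comparable with randomised arms.

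The stated adjustment is weak for this purpose. It depends on an observed imbalance, it names neither the baseline value of the primary outcome nor date of recruitment, and it is not explicit that it covers group 4.

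Group 4 also completes a 2x2 layout (PRCI yes/no by monitoring yes/no). Comparing it with each other group does not give the contrast that speaks to effect modification.

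PRCI Control against Routine Care resembles the PRCI as it would be used in practice. A confounded difference there could be quoted as efficacy, with the Discussion's reassurance as support.

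**Working it through.** **1. The plan's own figures.** Attrition: 99/0.80 = 123.75, rounded up to 124; 3 x 124 = 372. Both match. The 297 is roughly reproduced (302) by a fixed-effects F test with 4 numerator df (3 groups by 3 times), taking medium to mean f = 0.25, alpha 0.05 and power 95%. A one-way three-group F test gives 251. Either way the calculation covers the three randomised arms and no contrast involving group 4.

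**2. What the comparisons estimate.** Let 1 = PRCI Intervention, 2 = Monitoring Control, 3 = Routine Care, 4 = PRCI Control.
- 4 vs 3: PRCI effect without monitoring.
- 4 vs 1: monitoring effect given the PRCI.
- 4 vs 2: both factors change at once.
- Effect modification: (1 - 2) - (4 - 3). This is none of the three.

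**3. Evaluable numbers.** Applying the plan's 20% attrition to group 4 (an assumption): 110 x 0.80 = 88. Randomised arms: 99 each.

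**4. Precision and power**, in SD units, one outcome at one time point, equal SDs, two-sided 0.05, normal approximation.
- Interaction: SE = sqrt(3/99 + 1/88) = 0.204. The 95% CI half-width is 1.96 x 0.204 = 0.40.
- Power for a 0.5 SD interaction: 0.5/0.204 = 2.45, giving 69%. For 0.25 SD: 23%.
- With no attrition (124/124/124/110): 78% for 0.5 SD.
- With T1 adjustment at an assumed correlation of 0.5, SE = 0.204 x sqrt(0.75) = 0.177: 81% for 0.5 SD and 29% for 0.25 SD.
- Group 4 vs one arm: SE = sqrt(1/99 + 1/88) = 0.147; 0.5/0.147 = 3.4, giving 93% for 0.5 SD.

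**5. Illustrative effect of a shift in group 4.** Suppose selection or period moves the group 4 mean by b SD, with no true effect and no adjustment, at a single time point.

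| b (SD) | False-positive rate, 4 vs one arm | False-positive rate, interaction |
|---|---|---|
| 0.1 | 10% | 8% |
| 0.2 | 28% | 17% |
| 0.3 | 53% | 31% |

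The sizes of b are assumptions; the article gives no basis for any value. The interaction contrast carries the same shift, so it too is non-randomised evidence. A shift equally present at T1 would cancel from a group-by-time test, leaving only a difference in change over time to bias it.

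**The case against.** The other side has several sound points.

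- **Adjustment.** A reader might infer that the comparison is wholly unadjusted. It is not: covariates are foreseen where groups differ, and multi-level modelling is planned. What remains is that the adjustment is conditional, that its list omits T1 HADS and recruitment date, and that the modelling is aimed at attrition.
- **Repeated measures.** HADS is taken at T1, T2 and T3 in all four groups (Table 1). If the group 4 ANOVA uses the same repeated-measures design, a constant shift cancels. The wording leaves this open, and a different trajectory in another period would not cancel.
- **Purpose.** A reader might infer that the group was added to test an interaction that the plan then forgets. The Discussion words the aim as the PRCI effect free of monitoring, which group 4 vs Routine Care does target, though with possible confounding. The interaction is the worry behind the group, not a declared test.
- **Contrasts.** A single four-group ANOVA also fits the wording and could contain the 2x2 contrast, and an article may leave contrast lists to a fuller plan. That is fair. It does not touch the bias claim or the conflict on timing, which the article itself states.
- **Power.** A reader might infer that group 4 is simply underpowered because 88 is below 99. The 99 was never its target, and the pairwise comparison is well powered at 0.5 SD. The shortfall concerns only the interaction, for which the article makes no explicit power claim.
- **Safeguards.** Group 4 is recruited in the same way, gets the same information and is told that randomisation will occur. This limits self-selection on known allocation. It does nothing about calendar period.

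**Conclusion.** The point holds in this form. The group 4 comparisons have no fixed safeguard for non-random allocation, and the reassurance about written protocols and blinding is wrong for selection and calendar-period differences. The two statements on when the group was added conflict and must be reconciled. No stated comparison shows whether monitoring modifies the PRCI effect. On 99/99/99/88 evaluable, that contrast would be estimated to within about ±0.40 SD unadjusted, with about 69% power for 0.5 SD. These figures assume 20% attrition in group 4, equal SDs and a single outcome.

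A reader might take the 10%, 28% and 53% as the trial's actual error rates, or conclude that the RCT result is compromised. The documents support neither. The shifts are illustrative and apply to an unadjusted single-time-point comparison, and the primary comparison rests on the three randomised arms. Severity: should-fix.

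**What to change.** 1. Label every comparison involving group 4 as non-randomised and exploratory, and keep it out of the confirmatory conclusion.
2. Always adjust these comparisons, whatever the imbalance tests show, for T1 HADS, treatment type, age and previous cycles, and for treatment date where recruitment periods overlap. Where they do not overlap, date adjustment cannot separate period from group; say so.
3. Report the contrast (PRCI Intervention - Monitoring Control) - (PRCI Control - Routine Care) with its 95% CI, as exploratory.
4. Delete the statement that written protocols and blinding protect this group from systematic bias.
5. Limit the sentence on adequate power to the three-arm RCT, and give the expected precision for group 4 instead.
6. Reconcile Methods/Design and the Discussion on when the group was added, and state whether the controls are concurrent.

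Cost: changes to analysis and discussion text only. T1 HADS is in Table 1. Age is in the Background Information Form. Treatment type, past cycles and treatment dates come from the chart review described under Study measures. The downside is a weaker claim for group 4.
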